### Sample size

The IY-ASLD® program will be implemented in Child and Adolescent Mental Health Services at each site. In two of them (HMIM and HGUGM), parents of children with ASD will be recruited (*n* = 48), and in one site (HSJD), parents of preterm children with communication and/or socialization difficulties will be included (*n* = 24). Participating families will be randomly allocated to the TAU condition or to the intervention group within each site.

For the sample size calculation, we used the outcome parental stress, measured through the questionnaire Parental Stress Index Short Form (PSI-SF) [33]. This is a 36-item scale, with a range of 180 points. There is data showing that a decrease of 16.5 points in the total scale stress score can be seen after attending an IY program [34]. Given that this study will be conducted with parents of children presenting neurodevelopmental difficulties, we anticipated that the decrease in the PSI-SF score would be lower. We estimated the necessary sample size considering a power of 80%, *α* = 0.05, a difference between pre- and post-test of 10 points, and a standard deviation of 20 [35], using a paired-samples *t* test. We estimated 34 participants needed per arm of the study. Thus, we aim to recruit approximately 70 participants. The drop-out rate has not been included when calculating the sample size, considering that a sample of 70 participants is similar or larger than previous pilot or feasibility studies [31, 36] and in line with recommendations by the National Institute of Health Research [37]. Moreover, previous studies involving interventions with parents of children with neurodevelopmental disorders have reported low attrition rates [18, 31, 36].

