### Recruitment

Parents/caregivers will be recruited between January and March 2020 within the Child and Adolescent Mental Health Services of each hospital site, where patients have previously been assisted for their neurodevelopmental difficulties (Fig. 1). A leaflet with the inclusion and exclusion criteria will be handed out to clinicians working in the services. A short recruitment period has been anticipated, given that the study will be conducted in regional units with a high number of referrals and the study researchers work in close collaboration with clinicians. Clinicians will be asked to discuss the study with eligible families and will ask the families permission to be contacted by the study researchers. If they agree to be contacted about the project, a research assistant will call the family to discuss the study further. If the family is interested in participating in the study and meets the inclusion criteria, an appointment will be made with parents to sign the informed consent and to complete the pre-intervention assessment. During this visit, researchers will make sure that participants receive all the necessary information and have the opportunity to ask any questions. Participants will be able to discontinue the treatment sessions or drop out from the control group at any point at their request.

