### Data collection

Data will be collected at baseline (before performing randomization), right before the beginning of the intervention and after finishing the IY-ASLD® intervention. Due to the COVID-19 pandemic, the intervention has been postponed 6 months (from March 2020 to September 2020), and families will be re-assessed before the start of the group for an updated measure of parental depressive symptoms and stress. Parents consenting to participate (mother, father, or both) will be offered a hospital appointment before and after the intervention with a research assistant to complete the assessment, including self-report measures, children outcome measures, and a voice recording for the ASFMSS tool. If both parents participate in the study, they will fill out the children’s outcome measures together (by consensus) and the parental outcome measures individually. Those parents who discontinue or deviate from the intervention protocols will receive a telephone call from the research assistant to arrange further hospital appointments or to check if they are willing to complete the questionnaires for the main outcomes on the phone.

The timeline for participants’ enrollment, data collection, and the conduction of the intervention are scheduled in Table 1.

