### Data analysis

Descriptive analysis will be used for primary outcomes (e.g., recruitment rates, number of sessions attended by participants, proportion attending at least 15 out of 22 sessions, and proportion finishing the program). Attrition and satisfaction rates with the program will be also described.

Differences (if any) in baseline and descriptive variables between intervention and TAU conditions will be described. Between-site differences will be analyzed with the chi-square and independent samples *t* tests and will be controlled for in the main analyses.

For secondary outcomes, the analysis will follow an intention-to-treat basis. Regarding parental stress and depression, the assessment taken right before the intervention begins will be the one included in the analysis. Differences between the treatment groups in terms of parental levels of stress, expressed emotions, and parenting practices will be determined with the analysis of covariance (ANCOVA). Relevant confounding variables, such as socio-demographic variables, cognitive level at baseline, or treatment site, will be added as covariates. We will also estimate 95% confidence intervals and effect sizes [52]. Further secondary analysis will use similar methods to compare treatment groups regarding additional child outcomes (i.e., CBCL externalizing problems).

Missing data (i.e., missing item responses in questionnaires) will be treated following the instructions stipulated in the questionnaire’s manual. Imputation methods will be considered for full-case missing data. The analysis will be conducted using the SPSS/STATA statistical packages.

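### The only stated step for retrieving outcome data is tied to leaving the intervention; with no stated equivalent for TAU or for a missed close-out visit, missingness and assessment mode could differ by arm

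*Protocol article*

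**What the plan says.** Under Data collection, every consenting parent "will be offered a hospital appointment before and after the intervention with a research assistant to complete the assessment". That offer is not restricted by arm. The same section then adds one retrieval step: "Those parents who discontinue or deviate from the intervention protocols will receive a telephone call from the research assistant to arrange further hospital appointments". The sentence ends with an alternative purpose for the call: "or to check if they are willing to complete the questionnaires for the main outcomes on the phone".

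Under Recruitment, the article names two ways of leaving: "Participants will be able to discontinue the treatment sessions or drop out from the control group at any point at their request". The retrieval sentence takes up the first of these. No section gives a matching step for the second.

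Under Data analysis: "For secondary outcomes, the analysis will follow an intention-to-treat basis", with ANCOVA for the between-arm contrasts. On missing outcomes it says only that "Imputation methods will be considered for full-case missing data". Under Sample size: "The drop-out rate has not been included when calculating the sample size", partly because "previous studies involving interventions with parents of children with neurodevelopmental disorders have reported low attrition rates". No attrition figure is given.

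**The concern.** The trigger for the call is departure from the intervention protocols. The Intervention section describes a manualised programme of 22 online sessions for one arm. It describes TAU as outpatient care with unstructured input, so on a plain reading TAU has no protocol to discontinue or deviate from. A research assistant following the sentence literally would chase parents in one arm only.

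Three things could then differ between arms: the effort spent on obtaining outcomes, the share and type of families with missing outcomes, and the share of questionnaires completed by telephone. Families and clinicians know the allocation, and the questionnaire outcomes, including PSI-SF, are reported by parents. An intention-to-treat contrast needs outcomes sought in the same way from everyone randomised. The sample size holds no reserve for drop-out, and the handling of wholly missing cases is left open.

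The trigger has a second weakness. Stopping sessions is not the same event as missing the assessment. An intervention parent who attends every session but misses close-out is not covered by the sentence either.

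**Working it through.** **The plan's own figure.** The Sample size section uses a paired t test with a pre–post difference of 10 PSI-SF points, an SD of 20, α = 0.05 and 80% power. I take α as two-sided. The standardised effect is 10/20 = 0.5. The noncentral t calculation gives n = 33.4, rounded up to 34, which is the stated number per arm. The normal approximation gives 32. The figure reproduces. The point does not depend on it; it supplies only the 10-point yardstick, which is itself a pre–post difference and not a between-arm one.

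**Reading the text.**
- Standard assessment: same offer in both arms (Data collection).
- Extra call and telephone option: stated for departure from the intervention protocols (Data collection).
- Control-group drop-out: named as a separate event (Recruitment), with no retrieval step stated.
- Missed close-out visit as such: no retrieval step stated for either arm.

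**Size, by illustration.** The article gives no drop-out rate, retrieval rate or outcome difference for drop-outs, so all three are assumptions:
- d = share of an arm that drops out and would otherwise have no outcome: 10%, 20% or 30%, equal in both arms
- r = share of those retrieved: 50% or 80% in the intervention arm, 0 in TAU
- s = PSI-SF difference between drop-outs and completers: 5 or 10 points

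In one arm, the observed mean minus the full mean is d·r·s/(1 − d + d·r) − d·s. With equal d and no retrieval in TAU, the −d·s terms cancel, and the bias in the between-arm contrast is d·r·s/(1 − d + d·r).

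Example with d = 0.20, r = 0.5, s = 10: 0.20 × 0.5 × 10 / (0.80 + 0.10) = 1.0/0.90 = 1.11 points. With 35 per arm (70/2), observed numbers are 35 × 0.90 = 31.5 against 35 × 0.80 = 28.0.

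| d | s | bias, r = 50% | bias, r = 80% |
|---|---|---|---|
| 10% | 5 | 0.26 | 0.41 |
| 10% | 10 | 0.53 | 0.82 |
| 20% | 5 | 0.56 | 0.83 |
| 20% | 10 | 1.11 | 1.67 |
| 30% | 5 | 0.88 | 1.28 |
| 30% | 10 | 1.76 | 2.55 |

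The range is 0.3 to 2.6 points. The sign reverses if drop-outs are less stressed than completers. With r = 50% in both arms the bias is 0 under the same assumptions. These are unadjusted available-case figures; covariate adjustment or imputation could reduce them.

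**The case against.** The strongest reply is that the gap is read from silence. Nothing in the article says that TAU families will not be called. The word for protocols is plural and might be meant to cover both conditions, and an article may leave the handling of missed visits to a fuller document. This stands in part: a reader might infer that TAU families get no call, and the text does not establish that. But the article does state a rule with its trigger, and the trigger as worded fits only one arm, so the wording itself is open to correction.

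The second reply is that one-sided calls may reduce an imbalance. Only the intervention arm has 22 sessions to abandon, and the Primary outcomes section accepts that as few as 50% may finish. Suppose s = 10, with non-attendance of 30% in the intervention arm and 10% in TAU. Without retrieval the contrast is biased by (−0.30 × 10) − (−0.10 × 10) = −2.0 points. Retrieving two-thirds in the intervention arm alone gives 0.30 × (2/3) × 10/(0.70 + 0.20) − 3.0 + 1.0 = +0.2. This stands, and it is why the direction cannot be stated. It does not rescue the wording, because equal rates of missingness would not equalise who is missing or how they were assessed.

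Third, mode need not differ. The call's first purpose is to arrange a hospital appointment, and the telephone option covers main outcomes, a term that may not include PSI-SF, since the primary outcomes are feasibility measures. This also stands: a mode difference is possible, not certain.

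Finally, dropping out of the control group may mean leaving the study, in which case not pursuing the family respects its wish. A rule limited to families that have not withdrawn consent meets this.

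**Conclusion.** The point holds as a risk created by the wording. The stated retrieval step is attached to departure from the intervention, and no equivalent is stated for TAU drop-out or for a missed close-out assessment. Missingness and assessment mode could therefore differ by arm in the secondary comparisons. Under the assumed ranges (equal drop-out of 10–30%, one-sided retrieval of 50–80%, a 5–10 point difference) the bias is roughly 0.3 to 2.6 PSI-SF points, of unknown direction, against the 10-point planning difference.

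Three stronger readings are not supported:
- That missingness will differ by arm: every parent is offered the same post-intervention appointment, and the calls could offset a difference.
- That a retention comparison within the primary outcome is distorted: the article plans descriptive reporting of attendance, programme completion and attrition, and states no between-arm test of retention.
- That the bias could reach a large part of the planning difference: 4 points, for example, needs 20% drop-out, a full 20-point gap, and complete retrieval in one arm with none in the other (0.20 × 20 = 4). Nothing in the article supports such values, and it expects low attrition.

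The affected contrasts are secondary, in a pilot whose Discussion says it was not powered for between-group differences. This is a cheap improvement and not a threat to the feasibility aim.

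**What to change.** Reword the retrieval sentence so that the trigger is a missed post-intervention assessment, or stopping the allocated condition, in either arm. Apply it to every randomised family that has not withdrawn consent, with the same call and the same offer of telephone completion. Say which questionnaires the telephone option covers. Record for each assessment whether it was done in hospital or by telephone, and report missingness and mode by arm beside the secondary comparisons.

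The cost is a change of wording, one extra data field and a few more calls by the research assistant who already makes them. The downside is a slight contact burden on TAU families.

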### Data analysis

Descriptive analysis will be used for primary outcomes (e.g., recruitment rates, number of sessions attended by participants, proportion attending at least 15 out of 22 sessions, and proportion finishing the program). Attrition and satisfaction rates with the program will be also described.

Differences (if any) in baseline and descriptive variables between intervention and TAU conditions will be described. Between-site differences will be analyzed with the chi-square and independent samples *t* tests and will be controlled for in the main analyses.

For secondary outcomes, the analysis will follow an intention-to-treat basis. Regarding parental stress and depression, the assessment taken right before the intervention begins will be the one included in the analysis. Differences between the treatment groups in terms of parental levels of stress, expressed emotions, and parenting practices will be determined with the analysis of covariance (ANCOVA). Relevant confounding variables, such as socio-demographic variables, cognitive level at baseline, or treatment site, will be added as covariates. We will also estimate 95% confidence intervals and effect sizes [52]. Further secondary analysis will use similar methods to compare treatment groups regarding additional child outcomes (i.e., CBCL externalizing problems).

Missing data (i.e., missing item responses in questionnaires) will be treated following the instructions stipulated in the questionnaire’s manual. Imputation methods will be considered for full-case missing data. The analysis will be conducted using the SPSS/STATA statistical packages.

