### Randomization

Randomization will take place once all the participating families have completed baseline measures. Then, they will be randomly allocated to the intervention group or to the TAU condition within each center. Randomization will be conducted using the Program R 3.6.2 (R Foundation for Statistical Computing), generating a replicable process fixing a random seed. Allocation will be stratified by developmental level, considering two levels above and below IQ = 70 (assessed with cognition subscale of the Developmental Profile-3) [38].

An independent researcher will carry out the randomization process, and researchers who are responsible for patient recruitment or for intervention delivery will not be involved. Due to the pragmatic and clinically focused nature of the study, further blinding procedures will not be possible.

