## Discussion

The main aim of the study is to pilot the IY-ASLD® intervention in Public Mental Health Services in Spain. The current study has several strengths. Firstly, to the best of our knowledge, this is the first time that this program will be conducted in Spain. This is relevant in terms of improving the availability of treatments for children with neurodevelopmental difficulties within the Spanish Public Health System. Also, given that this intervention has been designed and tested in other countries (the USA and the UK), it is important to test if it can be implemented in Spain, where we have language, cultural, and healthcare system differences. Moreover, the IY-ASLD® program will be tested in different areas within Spain, providing a broad view of its feasibility across the country. Secondly, the present study targets a broad range of patients with early neurodevelopmental problems, as not only those meeting the diagnostic criteria for ASD are included, but parents of premature children with socialization and/or communication difficulties are also offered the intervention. Different strategies have been put into place in order to provide coherence and internal consistency to the study. Group leaders have attended the official training and will be following the procedures established in the program to assure fidelity to the intervention. Finally, preliminary efficacy will be analyzed, which could inform the importance of conducting a larger randomized controlled trial. Regarding limitations, the sample size might be limited in terms of power for some effect analyses, considering that the trial has not been powered for between-group differences. However, it is of note that we are introducing validated measures that go beyond parent-reported questionnaires to assess parent-child relationships (i.e., ASFMFSS), which is of paramount importance when evaluating parenting interventions and children in preschool years. Another limitation is the repetition of the assessment of parental stress and depression (due to the COVID-19 pandemic) once parents already know their group allocation.

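### The stress and depression scores chosen for the analysis are the September 2020 re-assessment, taken after parents knew their arm; the pre-randomisation scores should be the baseline covariate

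*Protocol article*

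**What the plan says.** All references are to the protocol article.

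- **Randomization:** "Randomization will take place once all the participating families have completed baseline measures". Table 1 lists PSI-SF and BDI at enrolment (January to February 2020) and puts allocation in March 2020. A pre-randomisation score therefore exists for both scales.
- **Data collection:** after the pandemic delay, "families will be re-assessed before the start of the group for an updated measure of parental depressive symptoms and stress". Table 1 dates this to September 2020 and the post-intervention assessment to May 2021. Only PSI-SF and BDI are repeated. The other outcome scales measured before and after have one pre-intervention score, taken before randomisation.
- **Data analysis:** for stress and depression, "the assessment taken right before the intervention begins will be the one included in the analysis". The next sentence names ANCOVA for stress, expressed emotions and parenting practices. On covariates it says: "Relevant confounding variables, such as socio-demographic variables, cognitive level at baseline, or treatment site, will be added as covariates". The secondary analysis is stated to be by intention to treat.
- **Discussion:** the repeat assessment is listed as a limitation because it happens "once parents already know their group allocation".

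**The concern.** A baseline covariate is safe in a randomised comparison because allocation cannot have influenced it. Any arm difference in it is chance, and adjusting for it removes noise without moving the expected arm difference. The September score lacks that property. It is a self-report, completed by parents who have known for months whether they will get the programme, in a trial without participant blinding. Relief in the intervention arm, disappointment in the TAU arm, or the reverse could move it. ANCOVA would treat such a movement as chance imbalance and subtract part of it from the arm comparison.

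At stake is the estimate for parental stress, which is the first secondary hypothesis and the outcome used to size the trial, and probably the estimate for depression as well. The limitation is disclosed, but the rule in Data analysis is unchanged by it.

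**Working it through.** **The plan's own figure.** Sample size gives a 10-point pre-to-post difference, SD 20, 80% power, α = 0.05 and a paired t test. The standardised difference is 10/20 = 0.5. Taking α as two-sided, n = 33.4, rounded up to 34 per arm, as stated. Nothing below depends on it, but it shows that the 10 points are a within-arm change.

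**Order of events (Table 1).** PSI-SF and BDI in January–February 2020; allocation in March 2020; PSI-SF and BDI again in September 2020, just before session 1; outcome in May 2021. The score selected for analysis comes about six months after allocation.

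**Size of the distortion.** Let *s* be the intervention-minus-TAU difference in the September score caused by knowing the arm, and *b* the within-arm slope of the May score on the September score. Then

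expected ANCOVA arm difference = effect of assignment on the May score − *b* × *s*.

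The second term is the distortion. The documents give neither *b* nor *s*, so both are assumed (*b* equals the correlation if the SDs at the two times are equal):

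| Assumed shift (absolute) | *b* = 0.5 | *b* = 0.7 |
|---|---|---|
| 0 points | 0 | 0 |
| 2 points | 0.5 × 2 = 1.0 | 0.7 × 2 = 1.4 |
| 5 points | 0.5 × 5 = 2.5 | 0.7 × 5 = 3.5 |

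The sign is open. If the intervention arm reports less stress in September because it expects help, the benefit is understated; if it reports more, the benefit is overstated.

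**Check by simulation.** 35 per arm, SD 20, no effect on the May score, 4,000 replicates. Assumed correlations: older score with May 0.5, older score with September 0.6, September with May 0.5 or 0.7.

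| Shift in September | Adjusting for September: mean estimate | Rejection rate | Adjusting for pre-randomisation score: mean estimate | Rejection rate |
|---|---|---|---|---|
| 0 | about 0 | 5% | about 0 | 5% |
| −5 | +2.5 to +3.6 | 9% to 17% | about 0 | about 5% |
| +5 | −2.5 to −3.6 | 9% to 18% | about 0 | about 4% to 5% |

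The estimates match −*b* × *s*. The simulation lets the shift act on September only. If it also reached May it would be part of the effect of assignment, and the same *b* × *s* would still be subtracted from that effect.

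**Cost of going back to the older score.** Ratio of standard errors = √[(1 − r_old²)/(1 − r_new²)]. With an assumed r_new = 0.7 for September, the denominator is 0.51:

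- r_old = 0.6: √(0.64/0.51) = 1.12
- r_old = 0.5: √(0.75/0.51) = 1.21
- r_old = 0.4: √(0.84/0.51) = 1.28
- r_old = 0.3: √(0.91/0.51) = 1.34

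The standard error rises by about 12% to 34%.

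**The case against.** The best defence of the plan is that the September score is more recent. Six months of pandemic lie between the two measurements, and the older score may predict May poorly. That stands as an argument about precision. It is not an argument about bias: pandemic changes common to both arms do not unbalance a randomised comparison.

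A second defence concerns the estimand. The May outcome is also an unblinded self-report. If knowledge of the arm shifts answers in September and still does so in May, adjusting for the older score leaves that shift in the estimate, while adjusting for September partly takes it out. This is correct, and the pre-randomisation score does not cure unblinded reporting. But the stated basis is intention to treat, so the target is the effect of assignment, and for that target the older score is the protected one.

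Several stronger readings are tempting, and the documents do not support them:

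- *The estimate is biased.* This is conditional. With no shift, either covariate is unbiased, and nothing in the article shows a shift.
- *The distortion can be expressed as a share of a 10-point target effect.* The 10 points are a within-arm pre-to-post change, and the Discussion says the trial was not powered for between-group differences. The article gives no between-arm target to divide by.
- *Families without a September score are excluded, against intention to treat.* Data analysis says imputation will be considered for full-case missing data, so exclusion is not the stated plan.
- *The article plainly makes September the covariate for both scales.* It says only that this score is included. The covariate role is inferred for both scales, and for BDI the ANCOVA is inferred too, because the ANCOVA sentence does not name depression.
- *No sensitivity analysis is planned.* A separate analysis plan may contain one; its absence from an article is not a fault.

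**Conclusion.** The point holds in a limited form. On its natural reading, the stated rule adjusts the stress comparison, and by inference the depression comparison, for a self-report taken after allocation was known, although a pre-randomisation score on the same scale exists. The possible distortion is about *b* × *s*: 0 to 3.5 PSI-SF points under an assumed slope of 0.5 to 0.7 and an assumed shift of 0 to 5 points, direction unknown. This is an illustration, not an estimate. Listing the problem as a limitation does not remove it while the rule stands.

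A reader might infer that the trial's main conclusion is at risk. It is not: the primary outcomes are feasibility measures analysed descriptively, and the Discussion makes a larger trial depend on those. The rule affects secondary, preliminary-effectiveness estimates, so this should be fixed but is not critical.

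**What to change.** Replace the sentence on stress and depression in Data analysis with, for example: *Post-intervention PSI-SF and BDI scores will be compared between arms by ANCOVA with the pre-randomisation score on the same scale as covariate. September 2020 scores will be reported by arm, and a model adjusting for them will be a sensitivity analysis.* This also settles the covariate role and the model for BDI.

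An alternative that uses all three time points is a constrained longitudinal mixed model: arms constrained equal at January–February, with September and May as post-randomisation outcomes. It recovers some of September's information without treating it as a baseline, and it keeps families who lack a September or May score under a missing-at-random assumption.

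Reporting September by arm shows whether knowledge of allocation was accompanied by a difference, though in a trial of about 70 families a small shift could go unnoticed.

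The cost is one sentence and no extra data collection. The pre-randomisation scores are already in hand; at the time of the article, the September and May scores were still to be collected. The statistical downside is the wider confidence interval worked out above.
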